### Recruitment procedure

Prior to the recruitment, a dedicated play corner will be established at each of the intervention health facilities and equipped with all the essential materials including age and developmentally appropriate play materials that will be used for providing stimulation intervention through play program. Intensive efforts will be undertaken to make the atmosphere in the SC room and the play corner relaxed, cheerful and welcoming.

In the 2 months recruitment period, health workers will screen children with SAM who will be shown up to the SC of the selected health facilities and recruit the first eight children with their mothers/ caregivers based on the study inclusion criteria. The health workers will discuss with the caretakers of all children fulfilling the inclusion criteria about the basic concepts of child nutrition, child growth and development and the details of the study including the involvement of the mothers/caregivers, the associated training need, about the required measurements and follow up procedures. Then, they will invite mothers/ caregivers to participate in the study with their child. After having received written informed consent from the mothers/ caregivers for their voluntary participation with their child, they will collect enrollment data.

### The intervention and follow-up

The intervention and follow up of the study subjects will take place for 8 months. In the intervention health facilities: children with SAM age 6–59 months will receive psychosocial stimulation in addition to the routine inpatient care in the SC and for 6 months after discharge through home-based follow up. In this study, the full WHO recommendations on emotional and physical stimulation [3, 7] will be implemented in the intervention health facilities. After the initial phase of treatment (Phase-I), children with SAM will participate in the psychosocial stimulation intervention at the regular schedule during the transition and phase 2 of the inpatient care and for 6 months after discharge through home-based follow up. In the SC, the child will spend prolonged periods on large play mats with other children, mothers and/or an intervention worker/ play guide on a daily basis to facilitate informal group play sessions. Each of the mother/ caregiver and their child will also participate in a half-hour of individual play sessions on a daily basis with an intervention worker/ play guide worker. Since, an average of 2–3 weeks are required to offer the full inpatient care (Phase 1, Transition Phase and Phase 2) in the SC, each child will receive about 12–19 individualized stimulation sessions in the SC after Phase 1 medico nutritional care. The play activities and toys will be selected to develop both motor and language skills considering the age and the level of child development. Accordingly, each play session will include language activities, motor activities, and activities with toys.

Toys will be always available in the child’s cot and room, as well as in the play area and they will be changed frequently. Inexpensive, safe and washable toys made from locally available materials such as cardboard boxes, plastic bottles, and tin cans and Western toys will be used. For those children who are unable to move, passive limb movements and splashing in a warm bath will be used to promote mobility. For other children, play activates will include rolling on a mattress, running after and tossing a ball, climbing stairs and walking. The duration and intensity of physical activities will be increased as the child’s nutritional status and general condition improve. A guiding curriculum with detailed play activities arranged by the age and the level of child development will be used to assist intervention workers/ play guides in the delivery of the intervention. The curriculum is prepared based on the Ethiopian protocol for the management of SAM [14] and recommendations of the WHO [3, 7]. The mothers/ caregivers will also be encouraged to play and chat with their children, asked for any questions they may have and given new skills and positive feedbacks to continue the activities between the scheduled stimulation sessions. They will be given complete information about the importance of adhering to the study procedures at discharge from the SC of the health facilities.

In the control health facilities, SAM children age 6–59 months will receive the routine inpatient care without psychosocial stimulation and home-based follow up for 6 months after discharge through home-based follow up.

In the 6 months follow up period after the discharge from the inpatient care, all children will be visited at home for five times at the end of 1st week, 2nd weeks, 1st month, 3rd months, and 6th months based on the recommended follow-up schedule of the WHO [3]. For the intervention groups, the intervention workers/ play guides will facilitate a half-hour individual stimulation session in each of the scheduled home visits where they will play with the child, the mother/ caregiver, and other family members if any. They will remind mothers/ caregivers on the importance of following study procedures and left extra play materials at home to enhance the interest of the child to the play activities.

The health education provided in Ethiopian public health facilities luck uniformity due to factors such as the absence of standardized training curriculum, health education manual and the variation in the training level of health providers. Therefore, mothers/ caregivers under both intervention and control group will also receive health education on the childcare such as child nutrition, child feeding, sanitation, and child growth and development during the inpatient care and for the period of 6 months after discharge. The health education manual consisting of key messages and the delivery schedule will be used to guide intervention workers in the delivery of uniform educational activities across all health facilities. The manual is prepared based on the available documents used in the Ethiopian context [11, 14–16].

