The reviewed studies have certain methodological issues that lead to very low-quality findings across important outcome indicators. A few of the limitations include the introduction of information contamination [6], the high level of lost to follow up (4,5&6), the lack of randomization [4].and unequal observation between the intervention groups [4]. Furthermore, in all of the reviewed studies, the full WHO recommendations on psychosocial stimulation [3, 7] were not implemented.

One of the goals of introducing stimulation and support intervention is to promote growth during the rehabilitation phase and to improve the treatment of severely malnourished children [8].

The reviewed studies did not adequately address the impact of the intervention on important treatment outcome indicators such as weight gain, duration of treatment, and the number of children discharged after recovery and the recurrence rate of malnutrition after discharge from the SC. Although positive findings have been observed from the few studies conducted in the area and the promotion of the stimulation intervention by organizations such as the WHO, the finding of a recent systematic review clearly indicated the need for further scientific evidence behind the inclusion of the stimulation intervention in the routine management of children with SAM [9].

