### Sample size determination and sampling technique

The sample size for the study is determined by considering the longitudinal (repeated measure from each subject over time) and clustered (study subjects nested in health facilities (clusters)) nature of the study. First, the sample size is determined by considering the longitudinal nature of the study using the formula for comparing two means [12] with the aim of detecting a 10% improvement from the mean + SD value of 15.8 + 4.4 for fine motor score of developmental domain which was obtained from similar study conducted in Ethiopia [6]. Four measurements are planned in the study. These include before the intervention when the child will be transferred from Phase I to the Transition Phase (baseline measurement), upon discharge from the SC of the health facilities and at three and 6 months. Thus, the number of time points of measurement taken from each study subjects; t = 4, type one error = 0.05, power = 90%, smallest meaningful difference d = 10% and the assumed correlation (r) of the repeated measures *r* = 0.02. Consequently, a sample of 44 children with the diagnosis of SAM satisfying the admission criteria to the SC per group will be required under individual randomization. The calculated sample size under individual randomization was further adjusted to account for the effect of clustering with an assumed Intracluster Correlation Coefficient (ICC) ρ = 0.05. Since this study is a trial with a fixed number of equal-sized clusters (k) the required sample size per group is obtained using the formula proposed by Hemming [13]. After considering, 20% of the calculated sample size for the potential dropout, 68 children will be required for each of the study groups. The corresponding number of individuals in each of the health facilities (clusters) is determined using the formula [13]. Accordingly, approximately eight study subjects from each of the study health facilities (clusters) will be required making the final sample 72 children with SAM for each of the study groups. Thus, 144 children with SAM age 6–59 months satisfying the inpatient admission criteria will be recruited and included in the two study groups. Based on the recommendation of Hemming [13] this trial is feasible since the number of clusters k = 9 per group is greater than the product of the number of individuals required under individual randomization (*n* = 44) and ICC (ρ = 0.05). Based on the report of the Silti Zone Health Office, the achievement of the target sample of children with SAM is feasible during the recruitment period.

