### Personnel for the study

Health workers who will be recruited from the SC of each of the health facilities will take the responsibility for the recruitment; follow up of children during the SC admission period, for supporting the intervention workers/play guides and for the collection of enrollment and other data. Depending on the caseload in the SC of the health facility, one or two health workers will be included in the study team from each of the health facilities.

For each of the health facilities, one young female intervention worker/ play guide who have completed at least grade 10 will be recruited from the local community considering their child-friendliness. In the intervention health facilities, the intervention workers/ play guides will assume the responsibility of facilitating the stimulation intervention during the inpatient care and for the period of 6 months after discharge through a home visit. They will also provide health education, conduct home-based follow up, collect follow up data, participate in the preparation of suitable toys from locally available materials, help mothers/ caregivers and other family members, and equip them with the essential skills for the implementation of the intervention. For each of the control health facilities, the intervention worker will only be responsible for providing health education, conducting home-based follow-up, and collection follow-up data. A separate mobile team of testers/ outcome assessors will be recruited considering their academic background and previous experience to collect anthropometric data and administer developmental tests. They will be unaware (Blind) to the allocation status of the children and the health facilities to avoid measurement bias.

Experienced supervisors will be recruited to oversee the activities of the health workers, the team of testers/ outcome assessors and the intervention workers. The field-level project coordinator under the direct guidance of the principal investigator will be responsible for the overall coordination and follow up.

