### Outcome measurement and tools

All outcomes will be assessed four times throughout the follow-up period. These include before the intervention when the child will be transferred from Phase I to the Transition Phase (baseline measurement), upon discharge from the SC of the health facilities and at 3 and 6 months where all mothers/ caregivers will be asked to bring their child to the health facilities for the latter two measurements. As per recommendations of the pilot study conducted to assess the feasibility and reliability of the sequence of various measurements, measurements requiring greater concentration (developmental tests) will be administered first that will be followed by the anthropometric measurements which will require less concentration [17].

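### The reminder to follow study procedures is written for intervention families only, although the 3- and 6-month outcomes depend on mothers in both arms choosing to attend the facility, so loss to follow-up may differ by arm

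*Protocol article*

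**What the plan says.** All references are to the protocol article.

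- **Home visits, intervention arm** (The intervention and follow-up). The passage opens: "For the intervention groups, the intervention workers/ play guides will facilitate a half-hour individual stimulation session in each of the scheduled home visits". The next sentence, about the same workers, reads: "They will remind mothers/ caregivers on the importance of following study procedures and left extra play materials at home".
- **Discharge talk** (same section). Mothers are to be told at discharge why adhering to the study procedures matters. This stands at the end of the description of the stimulation, before the paragraph on control facilities.
- **Control workers** (Personnel for the study). In control facilities, "the intervention worker will only be responsible for providing health education, conducting home-based follow-up, and collection follow-up data".
- **Late outcome tests** (Outcome measurement and tools). At 3 and 6 months, "all mothers/ caregivers will be asked to bring their child to the health facilities for the latter two measurements".
- **What both arms share** (The intervention and follow-up). On visits, "all children will be visited at home for five times at the end of 1st week, 2nd weeks, 1st month, 3rd months, and 6th months"; on education, "mothers/ caregivers under both intervention and control group will also receive health education on the childcare".
- **Dropout** (Sample size determination and sampling technique). One allowance is applied to each group: "After considering, 20% of the calculated sample size for the potential dropout, 68 children will be required for each of the study groups". No figure by arm is given.
- **Criticism of earlier studies** (Background of the study). The protocol lists high loss to follow-up and "unequal observation between the intervention groups" among their flaws.

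**The concern.** The 3- and 6-month tests carry the post-discharge effect on development and growth, and they are the protocol's scheduled outcome measurements for judging relapse after discharge. They need a voluntary trip to the facility. If the plan is followed as written, intervention families are told at discharge and reminded at home visits to follow study procedures, while no such prompt is described for control families. A prompt in one arm can raise attendance there for reasons unrelated to the child's condition.

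If attendance then differs by arm, and children who miss the tests differ from those who come, the two groups of completers are no longer comparable in the way that randomization provides. That is a bias, and a larger sample would not remove it. The protocol itself names high loss and unequal observation as weaknesses it wants to avoid, so a difference in prompting that serves no treatment purpose is worth removing before recruitment. The article says recruitment had not started at submission.

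**Working it through.** **1. What the reminder covers.** The text does not define *study procedures* in the home-visit sentence. Two readings are open.
- Narrow: carrying on the stimulation. The sentences around the reminder are about play sessions and play materials.
- Broad: including follow-up and measurement. Under Training of the study team, the study procedures for intervention-facility health workers include recruitment, data collection and facility-level follow-up. For play guides, the study procedures and the facilitation of stimulation are listed as separate items.

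The broad reading is at least as natural, so the words as written can prompt attendance at the tests.

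**2. The plan's sample size reproduces.** Inputs from the sample size section: mean 15.8, SD 4.4, difference 10% (d = 1.58), alpha 0.05 (taken as two-sided), power 90%, t = 4 measurements, r = 0.02, ICC 0.05, k = 9 clusters per arm, dropout 20%.
- Individual randomization: n = 2(1.960 + 1.282)² × 4.4² / 1.58² × (1 + 3 × 0.02)/4 = 162.97 × 0.265 = 43.19, so 44.
- Clustering: 44 × 9 × 0.95 / (9 − 0.05 × 44) = 376.2 / 6.8 = 55.3, so 56.
- Dropout: 56 × 1.2 = 67.2, so 68. Then 68/9 = 7.6, so 8 per cluster, 72 per arm and 144 in total.

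The plan's figures stand.

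**3. Power is not the issue.** With 72 per arm and the same inputs, a normal approximation gives the following for assumed losses (intervention/control):

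| Loss | Power |
|---|---|
| 20%/20% | 91.3% |
| 15%/25% | 91.3% |
| 10%/30% | 91.0% |
| 5%/35% | 90.6% |

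**4. Bias, as an illustration.** Two inputs are assumptions, not document figures: the split of loss by arm (kept at a 20% average), and g, the amount in SD units by which lost children score below retained ones, taken as equal in both arms. Within an arm, completer mean minus full-arm mean = loss × g × SD. The shift in the difference between arms is therefore (control loss − intervention loss) × g × 4.4.

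| Loss (intervention/control) | g | Shift (points) | Share of 1.58 |
|---|---|---|---|
| 20%/20% | any | 0 | 0% |
| 15%/25% | 0.25 | 0.10 × 0.25 × 4.4 = 0.11 | 7% |
| 15%/25% | 0.5 | 0.10 × 0.5 × 4.4 = 0.22 | 14% |
| 10%/30% | 0.25 | 0.20 × 0.25 × 4.4 = 0.22 | 14% |
| 10%/30% | 0.5 | 0.20 × 0.5 × 4.4 = 0.44 | 28% |

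With these signs, control completers look better than their full arm by more than intervention completers do, and the observed benefit shrinks. If lost children score higher, or if the intervention arm loses more, the sign reverses.

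**5. What the planned analysis changes.** The table is for an unadjusted comparison of completers. The protocol plans a mixed model on the repeated measurements, which uses the baseline and discharge scores of children lost later and can remove the part of the shift that those scores explain. At the protocol's own r = 0.02 that part is small; at a higher correlation it is larger.

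**The case against.** The case against is substantial.

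- **Contact is equal by design.** All children have five home visits, including months 3 and 6. Control workers also carry out home follow-up and collect data, and both arms receive health education for 6 months. An intention to stay in the area is an inclusion criterion in both arms. This stands, and it limits the risk.
- **The request to attend is common.** All mothers are asked to bring the child, and the required measurements and follow-up are explained at recruitment. This stands too. A reader might infer that retention effort is built into one arm only, or that attendance is compulsory; neither is what the document says.
- **The reminder may be about play.** This is possible, and the play materials are plainly part of the treatment. But the protocol's use of *study procedures* elsewhere is wider. If only play was meant, limiting the wording loses nothing.
- **The word *only* in the control workers' duties** contrasts them with play guides and does not forbid an appointment reminder. True, but nothing in the article assigns one.
- **A journal article leaves visit scripts to the full protocol.** Mere silence would be no finding. Here, though, the article states a prompt in one arm's text and a closed list of duties in the other's, so followed as written the arms differ.
- **The size is assumed.** This is right. No loss by arm, deficit among lost children or direction of bias is documented, and the mixed model would do better than the completer comparison.

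A reader might also take the loosely worded control sentence to mean that control children have no home visits. The statement that all children are visited, and the control workers' duties, settle that they do.

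**Conclusion.** The point holds in a limited form. The discharge talk and the home-visit reminder about study procedures are described for intervention families only, and the late outcomes in both arms rest on voluntary attendance. Loss to follow-up may therefore differ by arm. The stronger statement, that it is likely to, is not supported: visit number and timing, health education and the request to attend are shared, and the document has no loss figures by arm.

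The illustrative shift of 0.11 to 0.44 points rests wholly on the assumed loss splits and the assumed 0.25 to 0.5 SD deficit, applied to completers without adjustment. It shows what a moderate imbalance could do and is not a forecast. Nor does the document support concluding that a real benefit would be hidden, since the direction depends on who is lost. This is an inexpensive improvement to the conduct of follow-up and not a flaw that undermines the design.

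**What to change.** Separate attendance from stimulation in three places.

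1. In The intervention and follow-up, give caregivers in both arms the same discharge information on attending the 3- and 6-month tests, and the same attendance reminder at the shared home visits. The visits at weeks 1 and 2 and month 1 all fall before the 3-month test.
2. In Personnel for the study, add this reminder to the control workers' duties.
3. Limit the intervention-only reminder to the stimulation activities. The play materials stay as part of the intervention.

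Report loss at 3 and 6 months by arm, so that any remaining imbalance can be seen.

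The cost is one paragraph in the common visit guide and a minute or so per visit. Workers already make the same five visits in both arms, and the treatment contrast is unchanged.

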### Outcome measurement and tools

All outcomes will be assessed four times throughout the follow-up period. These include before the intervention when the child will be transferred from Phase I to the Transition Phase (baseline measurement), upon discharge from the SC of the health facilities and at 3 and 6 months where all mothers/ caregivers will be asked to bring their child to the health facilities for the latter two measurements. As per recommendations of the pilot study conducted to assess the feasibility and reliability of the sequence of various measurements, measurements requiring greater concentration (developmental tests) will be administered first that will be followed by the anthropometric measurements which will require less concentration [17].

### Primary outcome

The primary outcome of the study will be child development. The five areas of child development including personal-social, fine motor, language, gross motor, and social-emotional skills will be measured. The first four of the developmental dimensions will be measured using the Denver II-Jimma which is a culturally adapted, standardized and translated tool [18]. The tool was previously used in a number of studies to assess the developmental performance of Ethiopian children [19–21]. For each child, the performance score that refers to the sum of all items for each developmental domain will be calculated. The remaining social-emotional dimensions of the child development will be measured using parent completed Ages and Stages Questionnaire: Social-Emotional (ASQ: SE). The tool was adapted and translated for the Ethiopian context and used previously [19–21]. The child’s total score will be calculated by adding up the points of all items on the questionnaire.

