### Primary objective

To examine the effect of psychosocial stimulation interventions provided with the routine inpatient care and for 6 months after discharge on the development, growth and treatment outcome of children with SAM age 6–59 months in Southern Ethiopia.

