The model is appropriate for the present study considering the correlated nature of the repeated measurements from each study subject and from the hierarchical structure of data that study subjects nested in health facilities (clusters). In all the analysis variables with a *p*-value < 0.05 will be considered statistically significant.

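### The primary outcome is five separately scored domains with no lead domain or success rule; if any one at p<0.05 counts as success, the error rate is about 10–23%, not 5%

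*Protocol article*

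**What the plan says.** Under Primary outcome, the protocol article states that "The primary outcome of the study will be child development" and that "The five areas of child development including personal-social, fine motor, language, gross motor, and social-emotional skills will be measured". For the four areas tested with the Denver II-Jimma, "the performance score that refers to the sum of all items for each developmental domain will be calculated". The fifth area, social-emotional skills, comes from a different instrument, the ASQ:SE: "The child’s total score will be calculated by adding up the points of all items on the questionnaire". Data management and analysis repeats this scoring by dimension. Neither section combines the five scores or ranks them.

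The same analysis section plans a generalized linear mixed model for the overall effect of the intervention, allowing for repeated measurements and clustering. It closes with one criterion: "In all the analysis variables with a *p*-value < 0.05 will be considered statistically significant".

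The section on sample size aims to detect a 10% improvement in one score, using a mean and SD "for fine motor score of developmental domain which was obtained from similar study conducted in Ethiopia", with a type one error of 0.05 and 90% power.

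The Primary objective is to examine the effect "on the development, growth and treatment outcome of children with SAM age" 6–59 months. The Abstract and the outcome sections instead make development primary and growth and treatment outcome secondary.

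**The concern.** A primary outcome has to lead to one decision. Here it leads to five scores, each of which may be compared at 0.05, and the document does not say how five results become one conclusion. Some domains may reach significance and others not. The authors could then report an effect on child development from whichever domains succeeded, and nothing in the protocol would stand against it.

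Such a mixed pattern is plausible. The Background describes the earlier Ethiopian trial as improving gross motor function during the hospital stay and fine motor function, with a small effect, after discharge. At stake is whether a positive primary result would carry the 5% error rate for which the sample size was calculated.

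**Working it through.** **1. The plan's own sample size**

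Inputs from the sample size section: mean 15.8, SD 4.4, difference d = 10% of 15.8 = 1.58, t = 4 measurements, r = 0.02, alpha 0.05, power 90%, ICC 0.05, k = 9 clusters per group, 20% for dropout.

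- Single measurement: 2 × [4.4 × (1.960 + 1.282) / 1.58]² = 162.97 per group.
- Four measurements: 162.97 × [1 + 3 × 0.02] / 4 = 43.19, so 44. This is the plan's figure.
- Fixed number of clusters: n·k·(1 − ICC) / (k − n·ICC) = 44 × 9 × 0.95 / (9 − 2.2) = 55.3, so 56.
- Dropout: 56 × 1.2 = 67.2, so 68. Then 68 / 9 = 7.6, so 8 per cluster and 72 per group. Both match the plan.

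A one-sided 0.05 would give 35.2, so 36 rather than 44. The calculation therefore uses one two-sided 0.05 test of one outcome, fine motor.

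**2. Error rate across five domains**

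Assumptions: one two-sided 0.05 test per domain, no true effect in any domain, and any one significant domain counts as a positive primary result.

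If the domains are independent: 1 − 0.95⁵ = 22.6%.

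If the test statistics share a common correlation ρ, with c = 1.96:

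1 − ∫ φ(u) · [Φ((c − √ρ·u)/√(1−ρ)) − Φ((−c − √ρ·u)/√(1−ρ))]⁵ du

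| Assumed ρ | Chance of at least one false positive |
|---|---|
| 0 | 22.6% |
| 0.3 | 20.9% |
| 0.5 | 18.3% |
| 0.7 | 14.8% |
| 0.8 | 12.7% |
| 0.9 | 10.2% |

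Counting only results that favour the intervention (one-sided 0.025 each), the rate is 11.9% at ρ = 0, 9.1% at 0.5 and 7.4% at 0.7, against a nominal 2.5%.

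**3. Cost of keeping all five domains primary**

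The first step of Holm across five tests the smallest p-value at 0.05 / 5 = 0.01.

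- Standard error of the fine motor difference at the plan's n = 44: 4.4 × √[(2/44) × 1.06/4] = 0.483. The ratio 1.58 / 0.483 is 3.27.
- Power at 0.05: Φ(3.27 − 1.96) = 90.5%.
- Power at 0.01: Φ(3.27 − 2.576) = 75.7%.
- To restore 90% power at 0.01: 2 × [4.4 × (2.576 + 1.282) / 1.58]² × 1.06/4 = 61.2, so 62. After clustering, 62 × 9 × 0.95 / (9 − 3.1) = 89.8, so 90. With dropout, 90 × 1.2 = 108 per group, or 12 per cluster, against the planned 72.

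**The case against.** The strongest reply is that the protocol contains no rule under which one significant domain makes the trial positive. Its 0.05 criterion is a general threshold for significance, and the Hypothesis names development, growth and treatment outcomes together. If all five domains had to be significant, there would be no inflation. This is correct, and it makes the error figure conditional. It does not remove the point, because the text does not require all five either.

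A second reply is that multiplicity procedures are commonly left to a statistical analysis plan, which is not shown here. That would answer a complaint about silence. But the protocol does set an unadjusted threshold for every analysis, and choosing the primary endpoint is a matter for the protocol.

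Third, the documents give no correlation between domains, and a high one reduces the inflation. This stands, so a range is given. Even at 0.9 the rate is twice the nominal 5%.

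Fourth, fine motor may have been used for the sample size only because a mean and SD were available, and a composite or global test would stay closer to the stated construct. That is a fair alternative, but it would need its own definition and its own sample size.

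Two stronger readings are tempting. A reader might count fifteen tests, five domains at three visits after baseline. The documents do not support this: they plan a mixed model for an overall effect, and the sample size uses a repeated-measures formula, which points to one contrast per domain. A reader might also take the wider primary objective as further inflation. That objective is an umbrella which the secondary objectives split into its parts, and the outcome sections consistently make development primary. It is loose labelling and adds nothing to the error figure.

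**Conclusion.** The point holds in conditional form. The primary outcome has not been reduced to a testable endpoint, and the single 0.05 in the sample size does not match five separately scored primary domains each judged at 0.05. If any one domain suffices, the family-wise error is about 10–23%, for assumed between-domain correlations from 0.9 down to 0. This rests on one test per domain, each holding its own 5% level, with significance in either direction counted. That one domain suffices is an inference that the text permits, not a rule that it states. No claim is made about separate tests at each visit. The point concerns the trial's main conclusion and should be settled before recruitment.

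**What to change.** Name one primary endpoint: the Denver II-Jimma fine motor score, the domain already powered, tested by one overall intervention contrast from the planned mixed model. Make the other four domains secondary, with Holm adjustment across them. Reword the primary objective to match, and limit the general 0.05 criterion accordingly.

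This changes wording only and needs no more children; the article says recruitment had not started at submission. The downside is that a nominal p<0.05 in language, gross motor, personal-social or social-emotional skills no longer makes the trial positive. The choice must be fixed before any outcome data are seen by group, since a later choice could not be shown to be independent of the results.

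If all five domains must stay primary, apply Holm across the five and restate the power. At its first step fine motor power is about 76% with the planned sample, and restoring 90% at that step takes about 108 children per group instead of 72.
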